### Main outcomes

The resolution of clinical symptoms and interpretation of laboratory assays will be assessed in the study groups.

Clinical symptoms:FeverDry coughShortness of breathHeadacheMyalgiaOxygen saturationMortality rate

Laboratory markers:C-reactive protein (CRP)Malondialdehyde (MDA)Total antioxidant capacity (TAC)White blood cell (WBC)Neutrophils countLymphocytes countThe ratio of neutrophils to lymphocytesLevels of 25 hydroxyvitamin D and magnesium

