### Sample size

A total of 104 COVID-19 patients aged 18 to 65 admitted to the Shahid Mohammadi hospital in Bandar Abbas, Iran, who are eligible for the study are recruited. They are randomly divided into four groups of 26 subjects.

Based on the findings of the previous study [18], the sample size was calculated by the G*Power software, where the effect size for MDA variable was 0.68, alpha error probability was 0.05, power = 0.8, number of groups = 4, number of measurements = 2, and the assumed correlation among the repeated measures was 0.5. Then, taking into account the dropout rate of 0.1, the sample size in each group was estimated to be 26 patients.

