### Statistical analysis

The Kolmogorov–Simonov test will be used to check the normality of variable distribution. One-way ANOVA and Bonferroni post hoc tests will be used to analyze the differences between groups.

The mixed linear model will be used to estimate the treatment effect and the possible confounding variables will be adjusted in the model. IBM SPSS version 22 will be used for statistical analysis. *P*-value ≤ 0.05 will be considered a significant level in all statistical tests. To handle protocol non-adherence, the intention-to-treat (ITT) principle will be used to analyze data based on the original treatment assignment of the patients. Variables will be expressed as mean ± standard error or 95% confidence interval. The research team will not conduct interim analyses to stop or extend the trial because of the low-risk nature of the nutritional intervention in the present study. Indeed, early detection of the study hypotheses is unlikely and early termination of the intervention is not supposed to have any additional protection for patients.

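### Sixteen unranked main outcomes are all tested at 0.05 with no control across outcomes, although the trial was sized on MDA alone

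*Protocol article*

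**What the plan says.** Protocol article, Main outcomes: "The resolution of clinical symptoms and interpretation of laboratory assays will be assessed in the study groups". Two lists follow.

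- **Clinical (7):** fever, dry cough, shortness of breath, headache, myalgia, oxygen saturation, mortality.
- **Laboratory (9):** CRP, MDA, total antioxidant capacity, white cells, neutrophils, lymphocytes, the neutrophil-to-lymphocyte ratio, 25-hydroxyvitamin D, magnesium. The last two share one line.

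The abstract gives the same set. Neither place ranks the outcomes or calls one primary.

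Sample size: "the effect size for MDA variable was 0.68, alpha error probability was 0.05, power = 0.8". No other outcome enters the calculation.

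Statistical analysis: P ≤ 0.05 "will be considered a significant level in all statistical tests". The only correction is in this sentence: "One-way ANOVA and Bonferroni post hoc tests will be used to analyze the differences between groups". A second analysis is also planned: "The mixed linear model will be used to estimate the treatment effect".

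**The concern.** The Bonferroni step works among the four arms within one outcome and does nothing across sixteen. Followed as written, the rule lets each of sixteen outcomes reach significance on its own, and nothing says which one answers the trial's question. The sizing points to MDA, but the outcome list and the analysis section give MDA no priority. A report could then lead with whichever outcome crossed 0.05, and a reader could not tell a planned result from a selected one.

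Two of the sixteen are also different in kind. Under Intervention and comparator, groups A and B receive vitamin D, and groups A and C receive magnesium. Serum 25-hydroxyvitamin D and magnesium therefore reflect the supplements given. A rise in either shows exposure, not clinical or biochemical benefit.

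**Working it through.** **Plan's own figures.** The article gives no error rate across outcomes, so there is none to reproduce. Its 26 per group did not come out of the stated inputs under the repeated-measures readings tried. Taking 0.68 as Cohen's f gives 3 to 7 per group after 10% dropout, and taking it as d (f = 0.34) gives 6 to 29, none of them 26. That is a separate matter, and nothing below depends on it.

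**Inputs.** Outcomes: 7 + 9 = 16 (Main outcomes). Without the two serum-level measures: 16 − 2 = 14. Level per test: 0.05 (Statistical analysis). Completers per group: 26 × 0.9 = 23.4, taken as 23 (Sample size).

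**Step 1: one independent test per outcome, all nulls true.** The chance of at least one false positive is 1 − 0.95^k.

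- k = 16: 1 − 0.440 = 0.560
- k = 14: 1 − 0.488 = 0.512
- k = 13: 1 − 0.513 = 0.487

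The count of 14 is the fairer one, because the two serum levels are expected to move with supplementation and so are not true nulls.

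**Step 2: correlated outcomes.** Independence cannot hold exactly: the neutrophil-to-lymphocyte ratio is computed from two other listed outcomes, and the white-cell count contains both. Simulations used 23 per group, one omnibus F test per outcome and a common correlation between outcomes. The correlations are assumptions, and every outcome is treated as continuous. The last two columns count a false positive in either of two analyses per outcome: ANOVA on end values, and the group-by-time effect standing in for the mixed model, with a baseline-to-end correlation of 0.5.

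| Assumed correlation | 16 outcomes, one test | 14 outcomes, one test | 16 outcomes, both analyses | 14 outcomes, both analyses |
|---|---|---|---|---|
| 0 | 56% (formula) | 51% (formula) | 79% | 74% |
| 0.3 | 48–49% | 45–46% | 72% | 67% |
| 0.5 | 39% | 35–36% | 59% | 56% |

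Ranges come from two separate runs. At a correlation of 0.2, one test per outcome gives 52% for 16 outcomes and 48% for 14.

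**Step 3: what control would require.** If all sixteen stayed equal in rank, Bonferroni would need 0.05/16 = 0.0031 per outcome. With one primary outcome, the primary claim carries 5%, but only if its analysis and contrasts are fixed and their multiplicity is controlled. A four-arm factorial with two planned analyses can still yield several tests on a single outcome.

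**The case against.** A reader might infer that a chance positive result is more likely than not. The documents do not support that as a flat statement. The 56% needs sixteen independent true nulls, yet two outcomes are the supplemented substances and the blood-count outcomes are dependent by construction. With one test per outcome the figure drops below half at modest correlation. A further simulation built the white-cell count and ratio from their components and treated symptoms and mortality as binary, with assumed event rates. It gave 44–46% for 14 outcomes with everything else independent. The figure returns above half only when both planned analyses are counted. This objection stands against the phrase, not against the defect.

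A reader might also infer that a rise in 25-hydroxyvitamin D would make the trial positive. No section says so, and the stated aim covers clinical symptoms and inflammatory and oxidative stress markers, which serum levels are not. What remains is that the article lists them among its main outcomes under the same significance rule.

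The article describes itself as a summary, and the full protocol (Additional file 1) is not shown. That file may name a primary outcome, and handling of secondary outcomes is often left to such a document. So it cannot be said that the trial has no primary. But the article does more than stay silent: it ranks all sixteen equally, fixes one threshold for every test and sizes on one outcome. Those statements need correcting whatever the full protocol holds.

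Finally, MDA is a biomarker, while the title and aim put clinical symptoms first. That is fair, and the fix allows a clinical primary.

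**Conclusion.** The point holds. Sixteen outcomes of equal rank are tested at 0.05 with no control across them, and the outcome used for sizing has no priority.

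With one test per outcome, the chance of at least one false positive is 51% for 14 independent nulls and 56% if the two serum levels are counted as nulls. For all 16 outcomes it is about 39–49% at an assumed common correlation of 0.3–0.5. Against a nominal 5%, that is roughly eight times (39/5 = 7.8) to eleven times (56/5 = 11.2). Running both ANOVA and the mixed model on each outcome raises it further.

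The size rests on the global null and, beyond the independent case, on assumed correlations and continuous outcomes. The defect itself rests only on what the article states.

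**What to change.** Make these changes before the allocation code is broken. The Blinding section releases the code only after the statistical analysis, so the hierarchy should be fixed before that analysis is run.

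1. Name MDA at 3 weeks as the single primary outcome. If the sponsor prefers a clinical primary, state the sample-size basis for it.
2. Test it by one named analysis, the mixed model. Specify the treatment contrasts and control their multiplicity at 0.05 overall. For example, two factorial main effects under Bonferroni would be tested at 0.05/2 = 0.025 each.
3. Label the other outcomes secondary and report estimates with 95% confidence intervals. If significance is to be claimed, apply Holm to the whole secondary family: 16 − 1 − 2 = 13 outcomes with MDA as primary, so the smallest P is compared with 0.05/13 = 0.0038.
4. Report serum 25-hydroxyvitamin D and magnesium as exposure checks that cannot support an efficacy claim.
5. Replace the blanket P ≤ 0.05 rule with wording that matches this hierarchy, and update the registry.

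Recruitment was expected to end in August 2022 and the article appeared in February 2023, so the code may already be broken. If it is, the hierarchy should be reported as post hoc.

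The cost is wording in the protocol, registry and analysis plan, with no change to data collection. A clinical primary would also need its own sample-size justification. The downside is that fewer outcomes can be called significant.

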## Discussion

With the rapid prevalence of COVID-19 in recent years, more attention has been paid to effective dietary supplementation to improve clinical symptoms and biochemical parameters in these patients [19, 20]. To our knowledge, this is the first study to evaluate the effects of vitamin D supplementation in combination with magnesium or alone with respect to this infectious disease. The findings of the current RCT will provide evidence regarding the effectiveness of dietary supplementation strategies to improve COVID-19 outcomes.

## Auditing trial conduct

The Deputy of Research of Hormozgan University of Medical Sciences has appointed an independent person who is not a member of the research team to monitor the research's safety, scientific validity, and integrity from the initial setup to final reporting. For this purpose, a study progress report must be sent every 6 months, and after the monitor’s verification, the budget will be paid to continue the trial.

Protocol amendments will be communicated to all study investigators, coordinators, and trial sponsors. If any modifications are needed, these will also be updated in the trial registry (IRCT).

## Trial status

Ethical approval of the first version of the study protocol was obtained from the medical ethics committee of Hormozgan University of Medical Sciences, Bandar Abbas, Iran on May 30, 2021 (IR.HUMS.REC.1400.085). Currently, the recruitment phase is ongoing since August 23, 2021 and is anticipated to be complete by the end of August 2022.

## Trial registration

The study protocol was registered in the Iranian Registry of Clinical Trials (https://www.irct.ir; IRCT20210702051763N1) on August 14, 2021. https://www.irct.ir/trial/57413

## Data Availability

The final dataset of the trial will be available on request from the corresponding author via [contact], after obtaining the permission of the medical ethics committee.
